### Body composition analysis

Previous work in body composition by bio-electrical impedance in Ethiopian infants and children with SAM has shown that the conventional approach, predicting total bodyweight from height-adjusted impedance, fails due to confounding by oedema.^63^ The same project validated an alternative approach, known as Bio-electrical Impedance Vector Analysis, and described significant differences between each of three groups: healthy controls, oedematous-SAM and non-oedematous SAM. Vector analysis splits impedance into two height-adjusted components, resistance and reactance, which are further linked through phase angle (PA). Variability in these components is associated with biochemical parameters.^64^ These variables will be explored using graphical analysis or transformed into age-adjusted and sex-adjusted Z-scores for statistical comparison, including longitudinal analyses. Higher PA indicates better nutritional status, while declining height-adjusted resistance over time indicates loss of oedema.

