### Baseline procedures

Baseline data on maternal and household characteristics, the child’s medical history and current illness are collected by a study nurse. Anthropometry, including body composition measured by whole-body (wrist-ankle) bio-electrical impedance analysis (BodyStat 1500MD; BodyStat, UK), leg length using an electronic knemometer (Zimbabwe only, due to availability of knemometers) and triceps, subscapular and supra-iliac skinfold thickness using callipers (Holtain, Crymych, UK), are undertaken at baseline. Blood (1 mL/kg up to 5.4 mL maximum) is collected at baseline into an endotoxin-free EDTA tube for all children and, in the enteropathy substudy, additionally into a PAXgene tube (PreAnalytiX, Hombrechtikon, Switzerland) for subsequent transcriptomic analysis. Blood is not collected from children with severe anaemia (known haemoglobin <60 g/L). HIV testing is carried out in accordance with national guidelines as part of routine clinical practice; where it has not been done, the child’s HIV status is ascertained using a rapid test antibody algorithm for children over 18 months, or HIV DNA PCR for children under 18 months. CD4 count/percentage and viral load are measured in HIV-positive children. Maternal HIV status is documented where available, so that HIV-exposed uninfected children can be identified. Blood samples are sent to research laboratories at each site to conduct whole blood stimulation and bacterial binding assays (as described in the immunology substudy) and to store aliquots of whole blood, peripheral blood cells and plasma at −80⁰C.^31^ In the enteropathy substudy, nasogastric aspirate, stool and urine (after an oral dose of lactulose and mannitol) are also collected. Lactulose and mannitol are ingested by the child after fasting and urine is collected over a 2-hour period to measure recovery of lactulose and mannitol, a measure of intestinal absorptive capacity and permeability, as previously described.^32^

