### Daily procedures

Routine inpatient management is undertaken by ward clinical teams according to local hospital protocols, which are based on WHO guidelines.^2^
^33^ In addition, the HOPE-SAM study clinician at each hospital site collects daily data until discharge on clinical parameters (including daily examination), resolution of acute infections, nutritional recovery (loss of oedema, restoration of appetite, weight gain) and treatment/nutritional supplements received; this will allow us to evaluate differences in management between countries. Children with HIV-SAM who are ART-naive start ART according to national guidelines, which are based on WHO recommendations.^2 34^

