## Study outcomes and risk factors

The main study outcomes are clinical (mortality, morbidity and relapse of malnutrition) and nutritional (weight, height, MUAC, leg length, head circumference, mid-thigh circumference, skin-fold thickness and body composition by bioimpedance vector analysis) assessed over 48 weeks of follow-up. Mortality is assessed in hospital by daily physician review and, post discharge, through study visits and by telephone where possible for children who are lost to follow-up. Morbidity during hospitalisation is assessed through daily clinical assessments and available hospital laboratory tests. Morbidity after discharge is assessed, first, using daily morbidity diaries, in which caregivers record episodes of illness (lethargy interfering with feeding; respiratory distress; diarrhoea; oedema and fever); second, from caregiver recall and review of handheld medical records at each follow-up visit; and, third, from data collected during hospitalisation for children who are readmitted during the follow-up period. Time-to-recovery from malnutrition will be evaluated during hospitalisation; relapse of malnutrition during follow-up will be categorised as moderate acute malnutrition, uncomplicated SAM and complicated SAM, according to WHO definitions. Nutritional outcomes will be expressed both as continuous variables (attained Z-score and change in Z-score between visits), and as categorical variables (moderate wasting, WHZ<–2; severe wasting, WHZ<–3; stunting, HAZ<–2; severe stunting, HAZ<–3; underweight, WAZ <–2; and microcephaly, head circumference-for-age <–2).

Risk factors will be evaluated at baseline, hospital discharge and over the period of follow-up for associations with clinical and nutritional outcomes. In addition to baseline clinical and demographic factors, the following laboratory parameters will be evaluated: haemoglobin, serum albumin, C reactive protein (CRP), CD4 count and HIV viral load (for HIV-positive children). Haemoglobin, CD4 and HIV-viral load will be measured in real time and the results reviewed during follow-up clinics.

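### The body composition section reverses the reading of height-adjusted resistance: losing oedema fluid by itself raises it, so a decline is not evidence of oedema loss

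*Protocol article*

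**What the plan says.** The Study outcomes and risk factors section lists "body composition by bioimpedance vector analysis" among the main nutritional outcomes, assessed over 48 weeks. The Baseline procedures section describes the measurement as "body composition measured by whole-body (wrist-ankle) bio-electrical impedance analysis". Table 2 schedules it at baseline, at discharge and at all five post-discharge visits.

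The Body composition analysis section explains the choice of method. It says that the conventional impedance approach "fails due to confounding by oedema", and that the alternative works as follows: "Vector analysis splits impedance into two height-adjusted components, resistance and reactance, which are further linked through phase angle (PA"). These quantities are to be examined graphically or "transformed into age-adjusted and sex-adjusted Z-scores for statistical comparison, including longitudinal analyses". The section closes with two guides to interpretation. One says that a higher phase angle means better nutritional status. The other is that "declining height-adjusted resistance over time indicates loss of oedema". No other section gives a direction for resistance.

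**The concern.** Oedema is excess conductive fluid. Taking conductive fluid away leaves less material to carry the current, so resistance should go up. The protocol says that it goes down.

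What is at stake is the written interpretation of a longitudinal outcome. The method was chosen because oedema disturbs the conventional approach, so the oedema signal is the part that most needs to be read correctly. The Introduction also names the quality of tissue recovery, lean against fat, as a gap in knowledge. If the printed guide is followed, a fall in resistance that reflects fluid gain or regained lean tissue would be described as oedema resolving. A rise that reflects oedema resolving would not be recognised as such.

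**Working it through.** The protocol attaches no figure to this sentence, so there is none to reproduce. The check concerns the sign.

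**Inputs from the protocol article**
- The quantity is height-adjusted resistance, one of two named vector components (Body composition analysis).
- The measurement is whole-body, wrist to ankle (Baseline procedures).

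**Assumptions, not in the document**
- The body behaves as a single uniform conductor of length H, conductive volume V and resistivity rho.
- Fluid changes of 5% to 30%, height growth of 0% to 15% and the tissue changes below are illustrative ranges.

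**Relation.** R = rho × H² / V, so R/H = rho × H / V.

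**Step 1: fluid change alone (H and rho fixed).** A loss of fraction f multiplies R/H by 1/(1 − f); a gain multiplies it by 1/(1 + f).

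| Fluid change f | R/H after loss | R/H after gain |
|---|---|---|
| 5% | × 1.053 | × 0.952 |
| 10% | × 1.111 | × 0.909 |
| 20% | × 1.250 | × 0.833 |
| 30% | × 1.429 | × 0.769 |

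Loss raises R/H by about 5% to 43%; gain lowers it by about 5% to 23%. The sign is the same throughout the range.

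**Step 2: does growth rescue the sentence?** With 10% less fluid, R/H is multiplied by (1 + g)/0.90 for height growth g: × 1.111 at 0%, × 1.167 at 5%, × 1.222 at 10% and × 1.278 at 15%. Growth pushes R/H further up.

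**Step 3: does a change in resistivity rescue it?** For R/H to fall despite a fluid loss f at fixed height, rho would have to fall by more than the same fraction f. The protocol suggests no such mechanism.

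**Step 4: can R/H fall during recovery?** Yes, if conductive lean tissue is regained. With 20% more conductive volume and 5% more height, R/H is multiplied by 1.05/1.20 = 0.875. That fall contains no oedema loss.

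**Step 5: both processes together, at fixed height, as shares of starting conductive volume.** Oedema loss of 10% with lean gain of 20% gives V × 1.10 and R/H × 0.909. Oedema loss of 20% with lean gain of 10% gives V × 0.90 and R/H × 1.111. The net direction depends on which process dominates.

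**Step 6: the inverse index.** Under 5% to 30% fluid loss, H²/R is multiplied by 0.95 to 0.70. The printed direction would be right for that index.

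**The case against.** The best defence is that the sentence is a closing gloss and not an operating rule. No cut-off, endpoint or classification is built on falling resistance, and the estimates, tests and Z-scores are the same whichever way the sentence reads. All analyses are declared exploratory, and bioimpedance is one of eight listed nutritional measures. This stands, and it limits the reach of the error. It does not make the sentence right.

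A reader might infer that children whose oedema recurs would be classified as losing it, or that the oedematous versus non-oedematous contrast is compromised. The document does not support that. Screening and Table 1 define oedema by bilateral pitting on examination. In hospital, the Daily procedures section has the study clinician record "nutritional recovery (loss of oedema, restoration of appetite, weight gain"). After discharge, caregivers note oedema in the morbidity diary, a physician assesses the child at each visit, and relapse follows WHO definitions. Impedance decides none of this.

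A reader might also infer that the sign is wrong for every child. That goes too far: as step 5 shows, a child can lose oedema while R/H falls, because lean tissue returns at the same time. What is wrong is to attribute the fall to the oedema loss.

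Finally, the authors may have meant H²/R, since the section never writes the index as a formula. This reading is the weaker one, because resistance itself is named as the vector component. If it was intended, the text still needs to name the index.

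**Conclusion.** The point holds as an error of interpretation. Loss of oedema fluid by itself raises height-adjusted resistance, and a decline is compatible with fluid gain or lean-tissue accretion and is not evidence of oedema loss. The direction rests on the single-conductor relation with resistivity roughly constant, and it is the same across the whole range tried. The sizes, a rise of about 5% to 43% for an assumed 5% to 30% fluid loss at fixed height, are illustrations only.

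The consequence is confined to how longitudinal bioimpedance results are read and reported. Models, sample size, group definitions and the clinical record of oedema are unaffected. It merits correction because the protocol states the direction without qualification for a main outcome and nothing elsewhere corrects it.

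**What to change.** Replace the closing clause of the Body composition analysis section with wording such as: increasing height-adjusted resistance (R/H) over time is compatible with loss of oedema, and declining R/H with fluid gain or accretion of hydrated lean tissue; changes are read together with reactance, phase angle and clinically recorded oedema. If H²/R was intended, name that index explicitly; the stated direction can then remain.

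The cost is one sentence. It needs no new data and no change to the visit schedule, models or sample size, because the companion measurements are already planned. It should be made before the longitudinal bioimpedance results are interpreted.

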### Enteropathy substudy

The primary comparison for the enteropathy substudy will be between HIV-positive children with SAM (group A) and HIV-negative children with SAM (group C), stratified by presence or absence of oedema. Control groups (B and D) are well-nourished children with or without HIV, to provide normative data for biomarkers and to evaluate the impact of SAM within each HIV group. Thus, biomarkers among HIV-positive children with SAM will first be compared with HIV-negative children with SAM (to evaluate the impact of HIV) and, second, with well-nourished HIV-positive children (to evaluate the impact of SAM). Biomarkers among HIV-negative children with SAM will be compared with well-nourished HIV-negative children. For each continuous outcome, simple descriptive analysis will be used to compare groups during hospitalisation using t-tests on appropriately transformed data. For any outcome with moderate (p<0.05), evidence of difference between either group a regression model will be constructed including groups A, B, C and D to directly test (using interactions) whether there is a synergistic effect of HIV-SAM versus HIV-negative SAM versus HIV alone versus neither. These models will also be used to explore whether there is any evidence for heterogeneity in effects between oedematous and non-oedematous SAM. Associations between enrolment factors (eg, intestinal permeability and microbial translocation) will be explored using pairwise Spearman correlations and principal components analysis. Mean changes at the follow-up time points in each group will be estimated, and groups compared (as above) using generalised estimating equations. For outcomes that differ across SAM groups over time, multilevel models will be used to explore possible predictors from the other factors measured. Time to nutritional recovery will be compared using Kaplan-Meier and log-rank tests, and Cox models to adjust for baseline differences between groups.

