### Enteropathy substudy

The sample size was estimated using previously reported values for LM ratios, which remain a widely used non-invasive marker of enteropathy. Comparing 100 versus 100 children with two-sided alpha=0.025 (to allow for two primary comparisons, ie, HIV-SAM vs HIV-negative children with SAM, and HIV-SAM vs well-nourished HIV-positive children) provides >80% power to detect differences in mean LM ratio during hospitalisation of at least 0.16 (assuming SD 0.36), a difference which would be clinically relevant given the LM ratios previously reported for well-nourished children (0.42), malnourished children (1.3) and children with persistent diarrhoea (2.85) in the Gambia.^60^ It also provides >80% power to detect differences of at least 0.1 in the mean change in LM ratio from enrolment (assuming SD for change=0.23 and 7% missing samples). For inflammatory markers, comparing 100 versus 100 children with two-sided alpha=0.025 provides >80% power to detect differences in mean log_10_ concentrations of at least 0.44 times their SD, or 2.75-fold differences between groups. Inclusion of well-nourished controls provides an indication of normal ranges in young African children. HIV-positive and HIV-negative SAM groups will be stratified to include approximately 50 children with and without oedematous malnutrition, if possible.

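### The primary enteropathy comparison is called stratified by oedema, but the only in-hospital test named is a t-test with no stratum term; an oedema-adjusted linear model would fit the wording and keep the stated power

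*Protocol article*

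**What the plan says.** In the Analysis part of the protocol article, under Enteropathy substudy, the primary comparison is between "HIV-positive children with SAM (group A) and HIV-negative children with SAM (group C), stratified by presence or absence of oedema". For continuous outcomes during hospitalisation, the same paragraph states that "simple descriptive analysis will be used to compare groups during hospitalisation using t-tests on appropriately transformed data". A regression on groups A to D follows only for outcomes where a t-test gives p<0.05. Its stated purpose is to test for synergy between HIV and SAM, and it is also used to explore whether effects differ between oedematous and non-oedematous SAM.

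The Sample sizes part, under Enteropathy substudy, begins "Comparing 100 versus 100 children with two-sided alpha=0.025 (to allow for two primary comparisons", the first of the two being HIV-SAM against HIV-negative SAM. It says that this "provides >80% power to detect differences in mean LM ratio during hospitalisation of at least 0.16 (assuming SD 0.36"). On oedema it adds that "HIV-positive and HIV-negative SAM groups will be stratified to include approximately 50 children with and without oedematous malnutrition, if possible". Table 1 plans 50 children in each of A-I, A-II, C-I and C-II.

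The first hypothesis under Substudies, Enteropathy substudy, is that the degree of enteropathy during hospitalisation differs between the two forms of SAM.

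**The concern.** The comparison and the test do not fit together. A two-sample t-test of A against C cannot carry an oedema term, and the article does not say how the stratification enters. No oedema-adjusted estimate of A against C is specified for the in-hospital data. An outcome whose t-tests miss p<0.05 reaches no regression at all.

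Two things are at stake. First, if oedema affects the biomarker, as the protocol hypothesises, a pooled t-test leaves that variation in the error term and gives up precision. Second, the balance between A and C rests on a quota qualified as "stratified to include approximately 50 children with and without oedematous malnutrition, if possible". If the oedema mix ends up different in the two HIV groups, a t-test attributes part of any oedema effect to HIV.

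**Working it through.** **Inputs from the protocol article.** Difference in mean LM ratio 0.16, SD 0.36, two-sided alpha 0.025, 100 per HIV group (Sample sizes, Enteropathy substudy); 50 per HIV-by-oedema cell (Table 1). Power is from the noncentral t distribution.

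**1. Reproduce the plan's figure.**
- SE = 0.36 × √(2/100) = 0.0509; noncentrality = 0.16 / 0.0509 = 3.14; 198 df.
- Power = 81.1% (81.6% by the normal approximation). The stated >80% is confirmed for a pooled 100 v 100 comparison.

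**2. One contrast adjusted for oedema, all 200 children, 50 per cell.**
- With residual SD 0.36, the SE is again 0.0509, on 197 df. Power = 81.1%.
- If 0.36 is instead the overall SD with an even oedema mix, and oedema shifts the mean by e, the within-stratum SD is √(0.36² − e²/4).

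| Assumed e | Within-stratum SD | Adjusted power | Pooled t-test power |
|---|---|---|---|
| 0.1 | 0.357 | 81.9% | 81.1% |
| 0.2 | 0.346 | 84.4% | 81.1% |
| 0.3 | 0.327 | 88.4% | 81.1% |

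**3. Bias of a pooled t-test if the quota is missed.**
- Bias = (proportion oedematous in A − proportion in C) × oedema effect. With equal proportions it is zero.
- The documents give neither quantity, so these are assumed values, with the size of the bias shown:

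| Imbalance | Oedema effect | Bias | Share of 0.16 |
|---|---|---|---|
| 10 points | 0.15 | 0.015 | 9% |
| 10 points | 0.30 | 0.030 | 19% |
| 25 points | 0.15 | 0.0375 | 23% |
| 25 points | 0.30 | 0.075 | 47% |

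- With no true HIV effect and SE 0.0509, the nominal 2.5% rejection rate would become about 3.1% at a bias of 0.015, 5.1% at 0.030 and 22% at 0.075.

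**4. What adjustment costs under imbalance.** Residual SD 0.36, oedematous/non-oedematous in A v C:
- 40/60 v 50/50: 80.7%
- 60/40 v 40/60: 79.3%
- 25/75 v 50/50: 78.1%
- 70/30 v 30/70: 73.3%

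Adjustment removes the bias at a modest loss of power unless the imbalance is severe.

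**5. A contrast within one stratum, 50 v 50.**
- SE = 0.36 × √(2/50) = 0.072; noncentrality = 0.16 / 0.072 = 2.22; 98 df. Power = 48.1%.
- Difference detectable with 80% power: (2.241 + 0.842) × 0.072 = 0.22.
- This takes the within-stratum SD as 0.36. With e = 0.3 and within-stratum SD 0.327 (step 2), power is about 57%. So the 48% and the 0.075 bias rest on different assumptions and should not be combined.

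**The case against.** A reader might infer that the true power of the primary comparison is 48%. The documents do not support that. No section makes A-I v C-I and A-II v C-II the primary tests; the contrast is named at the level of groups A and C, and the power statement likewise compares HIV-SAM with HIV-negative SAM. A stratified comparison ordinarily means one estimate combined over strata, and this keeps about 81%. The sample-size paragraph also uses the word stratified for a recruitment quota, and carrying that sense into the analysis section leaves no conflict over power.

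A reader might also infer that the HIV contrast is confounded by oedema. That is not shown either. Enrolment is meant to continue until the Table 1 groups are filled, and at 50 per cell the pooled t-test is unbiased. The larger bias figures need both a sizeable imbalance and a sizeable oedema effect.

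It is fair to add that the t-tests are described as simple and descriptive, that regression, generalised estimating equations and multilevel models are also planned, and that the Analysis section treats all results as exploratory. How a stratum is coded is often left to a statistical analysis plan.

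What remains is narrower. The article itself fixes both the comparison and the test, and they do not match. Oedema enters the named in-hospital analysis only after a p<0.05 screen, and as heterogeneity rather than as adjustment. The exploratory label does not remove this, since the article still names primary comparisons and splits alpha for two of them. The immunology substudy, by contrast, explicitly adds oedema to its models.

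**Conclusion.** The point stands as an inexpensive improvement to the analysis, not as a failure of power. The >80% in the sample-size section is right and needs no correction. At 50 per cell, the loss from a pooled t-test is one of precision only: power of 81% against roughly 82% to 88% for oedema effects of 0.1 to 0.3, if 0.36 is the overall SD. If the quota is missed, the bias is the imbalance times the oedema effect, from 0.015 to 0.075 over the assumed range. Those inputs are illustrations; the documents support only the hypothesis that oedema matters and the conditional wording of the quota. The 48% describes a single within-stratum contrast and belongs in the plan only as a caution on secondary results.

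**What to change.** In Analysis, Enteropathy substudy, make the primary in-hospital comparison of A with C one linear regression of the transformed biomarker on HIV status plus an oedema term, fitted to all of about 200 children with SAM whatever the result of any preliminary test. Report the common HIV effect as the primary result. Label A-I v C-I, A-II v C-II and the HIV-by-oedema interaction as secondary or exploratory. Note that a 50 v 50 contrast at alpha 0.025 has about 48% power for 0.16, and detects about 0.22 with 80% power, if the within-stratum SD is 0.36. Leave the sample-size statement as it is.

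The cost is a change of wording and one degree of freedom. Oedema status is already recorded, since it defines the groups, and no extra children, samples or visits are needed.

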***Lactulose-mannitol (LM) testing will be conducted, with collection of a baseline urine sample, followed by a 2-hour urine collection post-LM ingestion. This test will be deferred until children are judged to be clinically stable by the study physician during daily reviews. In general, this will be a child in the nutritional rehabilitation phase, who has no cardiorespiratory compromise.

†††Skinfold thickness (triceps, subscapular, supra-iliac) and mid-thigh circumference will be measured using Holtain callipers or tape measure.

‡‡‡Body composition will be assessed by bioimpedance vector analysis.

Caregivers are reminded of follow-up visits by phone, and visit completion is tracked on a dedicated database. If caregivers do not attend follow-up appointments, attempts are made to contact them by phone and home visits are made if feasible, particularly for those defaulting on the 48-week visit, so that long-term outcome data can be collected. For post discharge deaths, a home visit is undertaken by study nurses where possible to conduct a verbal autopsy. Children who are readmitted to one of the study sites with relapsed SAM have data collected during the new episode of hospitalisation. The study ends for each participant at the week 48 visit.

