## Analysis

All analyses will be interpreted exploratively since HOPE-SAM is an observational study with multiple risk factors, outcomes and substudies. For all analyses, p values will not be artificially adjusted, but interpreted as exploring the strength of evidence supporting any association. The only exception is the use of approaches to minimise false discovery when analysing high-dimensional data from the microbiota and metabolomics substudies, as described.

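### The enteropathy HIV-by-SAM interaction is tested only after a screening t-test, which distorts the interactions reported and can hide real ones; separately, the 0.025 level used for sizing is not carried into the analysis

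*Protocol article*

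**What the plan says.** Groups (Table 1): A is HIV-positive with SAM, B is HIV-positive well-nourished, C is HIV-negative with SAM, D is HIV-negative well-nourished. Each has 100 children; A and C are 50 oedematous plus 50 non-oedematous.

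- **Sample sizes, Enteropathy substudy:** "Comparing 100 versus 100 children with two-sided alpha=0.025 (to allow for two primary comparisons". The two comparisons are A versus C and A versus B.
- **Analysis, opening paragraph:** all analyses are exploratory and "p values will not be artificially adjusted, but interpreted as exploring the strength of evidence supporting any association". The microbiota and metabolomics data are the only stated exception.
- **Analysis, Enteropathy substudy:** A versus C, stratified by oedema, is the primary comparison. A versus B and C versus D are also described. For continuous outcomes, "simple descriptive analysis will be used to compare groups during hospitalisation using t-tests on appropriately transformed data". The next step depends on the result: "For any outcome with moderate (p<0.05), evidence of difference between either group a regression model will be constructed". That model covers all four groups and examines synergy between HIV and SAM through interaction terms. No significance level is given for the interaction.

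**The concern.** Two separate matters arise.

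**The screen.** The interaction contrast is A − B − C + D. Each pairwise contrast that might open the screen uses two of the same four means. If the interaction is examined only when such a contrast is significant, its p value no longer has its nominal meaning and its estimate is selected. The wording does not settle whether A-C alone, A-C or A-B, or all three described pairs open the screen, and the size of the problem depends on that. A screen on pairwise differences can also stop a real interaction from being tested. The same models are to be used to explore heterogeneity by oedema, so that exploration depends on the screen too.

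**The level.** The sizing treats two comparisons as primary at 0.025 each. The analysis calls one comparison primary, gives 0.05 as its only threshold, and the general policy is not to adjust. A reader cannot tell at which level the two contrasts named in the sizing will be judged.

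**Working it through.** **1. The plan's own figure.** Inputs from Sample sizes, Enteropathy substudy: n = 100 per group, LM difference 0.16, SD 0.36, two-sided alpha 0.025. Normal approximation: power = Φ(δ√(n/2) − z), with δ = 0.16/0.36 = 0.444.
- At 0.025: Φ(0.444 × 7.071 − 2.241) = Φ(0.90) = 81.6% (81.1% with the noncentral t). The stated >80% reproduces.
- At 0.05: Φ(3.143 − 1.960) = 88.2%.
- Difference detectable with 80% power at 0.05: (1.960 + 0.842) × √(2/100) = 0.396 SD, or 0.396 × 0.36 = 0.143 LM units.

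**2. Correlation of screen and interaction.** With equal variances and equal n, let v be the variance of a group mean. Var(A − C) = 2v, Var(A − B − C + D) = 4v, covariance = 2v. Correlation = 2/√(2 × 4) = 0.71. A − B gives the same value; C − D gives −0.71.

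**3. Simulation.** 2 million draws of four normal group means (SE 0.1 SD, i.e. 100 per group), screen at 0.05, interaction tested at two-sided 0.05 (my assumption, as no level is stated). There is no true interaction in this table.

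| True effects | Quantity | A-C only | A-C or A-B | A-C, A-B or C-D |
|---|---|---|---|---|
| None | Outcome passes | 5.0% | 9.0% | 13.0% |
| None | False synergy among those passing | 34% | 30% | 29% |
| None | Passes and shows false synergy, over all outcomes | 1.7% | 2.7% | 3.7% |
| HIV 0.1 SD + SAM 0.1 SD | False synergy among those passing | 18% | 15% | 15% |
| HIV 0.1 SD + SAM 0.1 SD | Bias of interaction estimate among those passing | +0.22 SD | +0.20 SD | +0.05 SD |
| SAM 0.44 SD only | False synergy among those passing | 34% | 4.3% | 5.1% |
| SAM about 2.4 SD only | False synergy among those passing | 34% | 5.0% | 5.0% |

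The last row uses the LM means cited in the sizing: (1.3 − 0.42)/0.36 = 2.4 SD. Without a screen the interaction test has its nominal 5.0% throughout.

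**4. Missed interactions.** Take A = B = C, with D differing by 0.4 SD. Unscreened power is 52%. The screened procedure finds the interaction 2.5% of the time (A-C only) or 4.5% (A-C or A-B). If C-D also opens the screen it is 50%, so almost nothing is lost.

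**5. A stricter screen.** At 0.025 under no effects, false synergy among those passing is 39-43% over the three readings, higher than at 0.05. Tightening the screen is not a remedy.

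**6. Error over the two primary comparisons.** Treated as independent: 1 − 0.95² = 9.8% and 1 − 0.975² = 4.9%. Allowing for the shared group A, by simulation: 9.0% at 0.05 and 4.6% at 0.025.

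**The case against.** Passing the screen is an extra condition, so it cannot raise the chance that a given outcome yields a false synergy finding; it lowers it, to 1.7-3.7%. The 29-34% applies only to outcomes that pass, and under no effects the mean bias is zero. The cited LM means imply a SAM effect of about 2.4 SD; if A-B opens the screen, it then opens essentially always and nothing is distorted. The bias figure also depends on the reading: it falls from about +0.20 to +0.05 SD if C-D counts. All of this stands, and it bounds the point. It does not remove it: what will be read are the interactions tested, biomarkers with small effects are not protected, and the wording leaves the harmful A-C reading open.

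The article declares its analyses exploratory, and sizing at 0.025 while reporting unadjusted p values can be seen as conservative planning. The Analysis also lists A-C and A-B as its first and second comparisons, the same two as in the sizing. That softens the mismatch, but the level and the number of primary comparisons still differ between sections.

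A reader might also infer that the covariate-free t-tests leave the HIV contrast confounded. The document does not establish this. Covariate lists are commonly left to an analysis plan, the contrast is stratified by oedema, and no figure shows that A and C differ by age, site or timing. For the LM test, "This test will be deferred until children are judged to be clinically stable by the study physician during daily reviews"; that delay may itself result from HIV or enteropathy, so adjusting for it could remove part of the effect sought.

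**Conclusion.** The point holds in a bounded form. The screen distorts p values and estimates of the interactions that are reported: false synergy in 29-34% of passing outcomes with no effects and 15-18% with additive effects of 0.1 SD, but about 5% or less when SAM has a clear effect and A-B opens the screen. It can hide real interactions (52% down to 2.5-4.5% in the configuration shown, unless C-D counts). The undefined choice of pairs is a defect in itself.

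Two stronger readings are not supported. The screen does not raise the false-synergy rate over all outcomes. Nor does the unused 0.025 level cause the distortion, since a 0.025 screen makes it worse. The conflict over alpha is a separate inconsistency, worth about 9% against just under 5% error over two comparisons.

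The figures assume normal group means, equal variances, a full 100 per group and an interaction test at 0.05.

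**What to change.** 1. In Analysis, Enteropathy substudy, drop the p<0.05 condition. Fit one four-group linear model (HIV, SAM, HIV × SAM) for every listed biomarker, and read A-C, A-B and the interaction from it. Age band and site, already collected, can be added as covariates. Days from admission to the LM test should not be a default covariate.
2. Make the three sections agree on the primary comparisons and the level. Either judge the two primary LM contrasts at 0.025 each and list this as a further exception in the opening Analysis paragraph, or restate the sizing at 0.05 (detectable difference about 0.40 SD, 0.143 LM units) and keep the no-adjustment policy.

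The cost is analysis wording, a few degrees of freedom and, under the first option, a stricter threshold on two contrasts. No change to recruitment or data collection is needed.
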